### Joint Mediated Effects

An imputation-based approach using a class of natural effect models introduced by Lange et al [82] and Vansteelandt et al [83] will be used to estimate the joint mediated effect of all mediators simultaneously. We will use the “neModel” function [78] to compute the natural indirect effect (NIE), natural direct effect (NDE), and the TE. We will use 1000 bootstrapped simulations to estimate 95% CIs.

### Missing Data

We will assess the proportion and patterns of missing mediator and outcome data. We will conduct all analyses on complete cases if the proportion of missing data is less than 15% for all variables in a given model. If missing data exceed 15%, we will impute missing data through multiple imputation by chain equations using the “mice” package [84] in R.

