### Mediators, Outcomes, and Confounder

#### Overview

Patient characteristics, outcome measures, mediators, and potential confounders were assessed at baseline. Mediators were assessed again following the twelfth treatment session, approximately 12-18 weeks following allocation. Outcome measures were assessed again 18 weeks following allocation. Participants and outcome assessors were blind to group allocation and study hypotheses.

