#### Confounders

We assumed no confounding of the treatment–mediator and treatment–outcome relationships due to random allocation of treatment. We identified potential confounders of the mediator–outcome relationship using the disjunctive cause criterion [53,54]. This involved selecting measured pretreatment covariates that are hypothesized to be a cause of the mediator, outcome, or both. The minimum sufficient adjustment set includes age, biological sex, duration of LBP episode, number of previous LBP episodes, number of other painful areas, work status, injury compensation, education level, depression, concern of LBP severity, sleep difficulty, and pain biology knowledge (refer to Multimedia Appendix 1 for details on potential confounders). We will also include pretreatment measures of the mediators and outcomes in the models [55].

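### The 15% missing-data rule is applied variable by variable, so complete-case models with 16 or 28 variables can drop more than 15% of participants with no limit stated

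*Protocol article*

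**What the plan says.** The Missing Data section of the protocol article first promises a description of the gaps: "We will assess the proportion and patterns of missing mediator and outcome data". It then fixes the method. Analyses use "complete cases if the proportion of missing data is less than 15% for all variables in a given model". Otherwise, "If missing data exceed 15%, we will impute missing data through multiple imputation by chain equations".

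The models carry more than mediators and outcomes. The Confounders section lists "age, biological sex, duration of LBP episode, number of previous LBP episodes, number of other painful areas, work status, injury compensation, education level, depression", then "concern of LBP severity, sleep difficulty, and pain biology knowledge", and adds: "We will also include pretreatment measures of the mediators and outcomes in the models". Under Statistical Analysis, the outcome model contains the 18-week outcome, the mediator at baseline and follow-up, treatment and the confounders. The mediator model contains only the follow-up mediator, its baseline value and treatment. Under Joint Mediated Effects, all seven mediators enter one analysis.

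Two further statements bear on bias. The Overview of measurements says: "Mediators were assessed again following the twelfth treatment session, approximately 12-18 weeks following allocation". The Confounders section says: "We assumed no confounding of the treatment–mediator and treatment–outcome relationships due to random allocation of treatment". The Sensitivity Analyses section covers unmeasured confounding and the time order of mediator and outcome. It contains nothing on missing data.

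**The concern.** The threshold is checked on each variable, but a complete-case fit loses the union of the gaps across all of them. A rule that looks like a 15% cap on loss is therefore not one, and the more variables a model has, the weaker the protection.

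Two things are at stake. The first is precision: mediated effects from 276 people are to be estimated with bootstrap intervals, and participants with one missing baseline item would be discarded although most of their data are present. The second is possible bias. The appeal to randomisation covers everyone randomised. It does not automatically cover a subset defined by having follow-up data. Because the rule works model by model, some of the 14 mediator-outcome pairs (7 × 2) could also be analysed on complete cases and others on imputed data.

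**Working it through.** The 15% is a chosen threshold with no derivation, so there is no figure of the plan to reproduce. The check is what the rule permits.

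**Inputs from the article.** 276 randomised (Results); 7 mediators (Mediators); 12 confounders (9 + 3, Confounders); model terms (Statistical Analysis, Joint Mediated Effects). Missing rates: none given, so every rate below is an assumption.

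**Step 1: variables that can be missing** (treatment excluded, since it is always known).
- Single-mediator analysis: outcome at 18 weeks 1 + follow-up mediator 1 + baseline mediator 1 + baseline outcome 1 + confounders 12 = 16. Of these, 14 are pretreatment and 2 are follow-up.
- Joint analysis: 1 + 7 + 7 + 1 + 12 = 28, taking only the baseline value of the outcome being modelled. Of these, 20 are pretreatment and 8 are follow-up.
- Mediator model on its own: 2.

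**Step 2: share of participants lost.** With k variables each missing in a share p, the loss is p if the same people miss everything, 1 − (1 − p)^k if gaps are independent, and at most min(1, k·p).

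**Step 3: numbers.** In every row each variable is under 15%, so the rule selects complete cases.

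| Assumed missingness | 16 variables: lost (n kept) | 28 variables: lost (n kept) |
|---|---|---|
| Baseline complete, follow-up missing together, 14.9% | 14.9% (235) | 14.9% (235) |
| Each variable 1%, independent | 14.9% (235) | 24.5% (208) |
| Follow-up together 10%, each baseline item 1% | 21.8% (216) | 26.4% (203) |
| Follow-up together 14.9%, each baseline item 1% | 26.1% (204) | 30.4% (192) |
| Each variable 2%, independent | 27.6% (200) | 43.2% (157) |

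Third row in full: 1 − 0.90 × 0.99^14 = 0.218, and 1 − 0.90 × 0.99^20 = 0.264.

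In reverse, a true cap of 15% of participants means keeping at least 235 people (0.85 × 276 = 234.6). With independent gaps that corresponds to 1 − 0.85^(1/16) = 1.0% missing per variable, or 1 − 0.85^(1/28) = 0.6%, not 15%.

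**Step 4: does the loss bias the effects?** An illustrative simulation (400 replicates of 2,760 people, 35% lost, linear models, both models fitted to the same complete cases) had a true mediated effect of −0.20 and a true direct effect of −0.20.
- Missing completely at random: −0.20 and −0.20.
- Missingness depending on treatment and a covariate adjusted for in both models: −0.20 and −0.20.
- Missingness depending on the outcome and treatment: −0.16 and −0.10.

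The second result needs the covariate in both models. The planned mediator model adjusts only for treatment and the baseline mediator. If missingness differs by arm and depends on one of the 12 confounders that also affects the mediator, that model does not have this protection.

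**The case against.** The strongest reply is that most of the counted variables cannot disturb randomisation. Fourteen of the 16 and 20 of the 28 are pretreatment, so a gap in them does not result from the treatment received, and dropping that person costs precision only. This stands. A reader might infer that the complete-case set is in general a non-randomised subset with biased effects. The documents do not support that: only the 2 or 8 follow-up variables can select participants after allocation, and whether they do so harmfully depends on a missingness mechanism the article does not describe.

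A reader might also infer that most of the sample will be lost. Independent 5% gaps in every variable would keep 0.95^16 = 44% and 0.95^28 = 24% of participants. That requires age and sex to be as incomplete as a follow-up questionnaire, and gaps to be scattered at random. No rate in the article supports it, and follow-up items collected together are likely to be missing together.

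It is likewise tempting to say that people who stopped treatment early have no mediator data. The Overview says when mediators were measured. It does not say that those who stopped were not measured. Nor does the article plan a formal comparison between mediators, so mixing complete-case and imputed analyses is untidy but defeats no stated test.

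Finally, the article promises to inspect missing-data patterns and already names an imputation method, and a fuller plan might define the analysis sample. But the rule in the article is a definite instruction. Followed exactly, it allows the losses tabulated above, and inspecting the patterns triggers no change of method. That inspection is also promised only for mediators and outcomes, although confounders count towards the trigger.

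**Conclusion.** The point holds as a statement of what the rule permits. Complete-case analysis is chosen whenever each variable is under 15% missing, yet the share of participants dropped can exceed 15% and is not limited. Under a mild assumed pattern (follow-up missing together at 10%, each baseline item at 1%) the loss is 21.8% in a single-mediator analysis and 26.4% in the joint analysis. With a complete baseline and fully overlapping dropout it stays under 15%. The actual loss cannot be known from the article.

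The usual cost is precision. Bias is possible, not certain. It arises if missingness of the follow-up mediator or outcome depends on the outcome, or on causes of it that the fitted model leaves out, and the sparse mediator model makes the latter easier. It would not be removed by a better threshold alone, since it can occur with a loss below 15%. The lack of any missing-data sensitivity analysis means it would also go unexamined. This is a worthwhile, inexpensive improvement to the plan rather than a demonstrated error in its results.

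**What to change.** Replace the threshold rule with text along these lines: *Multiple imputation by chained equations on all 276 randomised participants is the primary analysis for every model, whatever the proportion missing. The imputation model includes all baseline and follow-up mediators, both outcomes at both times, and all confounders. It preserves the treatment × mediator interaction, for example by imputing within arm. Complete-case analysis is reported as a sensitivity analysis.*

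At minimum, apply the 15% to the share of participants with any missing variable in the model, and say which method applies at exactly 15%, which the present wording leaves open. This smaller change closes the gap in the rule but does not address bias at lower loss.

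The cost is wording, plus computing and pooling: imputation has to be combined with 1000 bootstrap samples across 14 single-mediator analyses and the joint analyses, and with the planned sensitivity analyses. The imputation package is already named in the plan. The Results section says the authors were still blind to the data, so at that stage the change could be made without knowledge of results.

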### Sensitivity Analyses

We will conduct sensitivity analyses to determine the robustness of the estimated ACME to bias introduced by unmeasured pretreatment confounding in the independent mediated effect models [85]. We will use the “medsens” function [80] to estimate the magnitude of residual confounding that would cause the point estimate of the ACME to reach 0. The level of residual confounding is represented by the correlation between the residuals (error terms) in the mediator and outcome models, denoted *ρ*. By estimating the ACME, including point estimates and 95% CIs, at all possible levels of *ρ* (between the extremes of –1 and +1), we can determine how strong the effects of residual confounding would need to be to reduce the ACME to 0 (ie, no mediating effect).

We will conduct a sensitivity analysis to determine the robustness of the estimated NIE and NDE to possible unmeasured confounding in the joint mediated effect model [85]. The mediational E-value [86] will be used to assess the minimum strength of the relationship between an unmeasured confounder and the mediator, conditional on measured confounders, that would reduce the NIE and NDE to 0. A comparatively large E-value in relation to known confounders implies that considerable unmeasured confounding would be required to reduce the NIE and NDE to 0. A comparatively small E-value implies that little unmeasured confounding would be required to reduce the NIE and NDE to 0. We will use the “EValue” package [87] in R to estimate the mediational E-value.

If appropriate, we will conduct a sensitivity analysis to assess possible violations to the temporal ordering of the mediator–outcome relationship, excluding participants for whom the mediators and outcomes were assessed concurrently at 18 weeks.

### Secondary Analyses

If there is evidence of a mediator–outcome effect, we will investigate the magnitude of change required in the mediator(s) to produce a minimally clinically important difference (MCID) in pain intensity (of 1 point out of 10) [88] and disability (of 2 points out of 24) [89].

### Ethics Approval and Consent to Participate

The University of New South Wales Human Research Ethics Committee granted ethical approval (HC15357), and all participants provided written informed consent to participate.

## Results

A total of 276 participants have been randomized into the RESOLVE trial. Follow-up data collection is underway with authors blind to study data.

## Discussion

We present an analysis plan for a mechanism evaluation of a new complex treatment strategy combining pain education and graded sensorimotor precision training (RESOLVE), when compared with a sham treatment in people with CLBP. The RESOLVE treatment constitutes a new paradigm for CLBP management with potentially wide-reaching implications. This mechanism evaluation will provide evidence for the hypothesized treatment mechanisms. If the treatment is effective, this investigation will help explain how the treatment worked, and if the treatment is ineffective, it will help explain why the treatment did not work. These results will help adapt and refine the treatment and guide future implementation strategies.

## Appendix

Multimedia Appendix 1 Potential confounders.

## Abbreviations

ACME: average causal mediation effect
ADE: average direct effect
ATE: average total effect
BBQ: Back Beliefs Questionnaire
CLBP: chronic low back pain
FreBAQ: Fremantle Back Awareness Questionnaire
LBP: low back pain
MCID: minimally clinically important difference
NDE: natural direct effect
NIE: natural indirect effect
NRS: Numeric Rating Scale
PCS: Pain Catastrophizing Scale
PSEQ: Pain Self-Efficacy Questionnaire
RCT: randomized controlled trial
TE: total effect
TSK: Tampa Scale for Kinesiophobia
